###### Analytic Approach

Mean inpatient opioid use, prescription size, postdischarge opioid use (in OME), and mean postsurgical health care utilization days will all be compared between groups using two-tailed *t* tests. Individual health care utilization outcomes will also be compared separately with two-tailed *t* tests for continuous data and chi-square tests for categorical data.

#### Aim 3: Qualitatively Evaluate the Effectiveness of the Comfort Coach Intervention

We will perform semistructured one-on-one interviews with 50 patients who had a comfort coach to understand (1) their experience with and perceived role of the intervention on their surgical experience and (2) the acceptability of the intervention. Insights from this thematic analysis will guide the identification and development of tools for broader implementation.

##### Semistructured Interviews

Interviews will be conducted by 2 study members (AB and MB) either in the FCVC cardiac surgery outpatient clinic area or over the telephone. Interviews will be audio recorded on an encrypted recorder, transcribed verbatim by an external HIPAA (Health Insurance Portability and Accountability Act)–approved professional transcriptionist, and redacted for all identifying information. Participants will be compensated with a gift card for their participation. After March 14, 2020, interviews were exclusively performed over the phone because of human subject research restrictions owing to the COVID-19 pandemic.

##### Analytic Approach

An initial interview guide will be developed and modified during the interview period through iterative steps. Data will be coded in MaxQDA20 (VERBI Software, 2019) qualitative analysis software. The team will meet to examine codes and identify emerging patterns and concepts that will be organized into themes. We will use the thematic analysis framework [68] to identify themes among patients who received a comfort coach and categorize these themes into 3 broad categories: (1) the role of the coach, (2) the impact of the coach, and (3) the acceptability of coaching. The data generated from these interviews will inform subsequent refining of our coaching intervention and development of tools for broader implementation of the intervention.

##### Power Analysis

Our primary endpoint is composite of health care utilization, defined as the total number of days spent at home within the first 30 days after surgery. Secondary endpoints include mean GAD-7 and PHQ-9, KCCQ-12, Picker Patient Experience Questionnaire, IES-R, and Brief Pain Inventory Scores and mean inpatient and outpatient opioid use.

We will compare mean days with a two-tailed *t* test and set the power of this study at 80% with alpha (Type I error) of .05 and the Cohen *d* effect size (defined as the difference in means divided by standard deviation) between medium (0.5) and large (0.8) [69,70], which yields a minimum sample size of 52 patients to detect a large effect size and 128 to detect a medium effect size [71]. Incorporating 20% missingness, a sample size of 154 patients will adequately detect a medium effect size. We next verified this statistically derived sample size with clinically relevant examples. Although most large series reporting opioid use report the median and interquartile range of OME [47,72], our sample size should be sufficient to satisfy the central limit theorem and use mean values. At our institution, the mean opioid use after sternotomy in 2017 was 200 OMEs. We estimated that to detect a 30% reduction in opioid use (mean 140 OMEs) with a standard deviation of 125 OME in the control and 100 OME in the intervention arms, a sample size of 114 would be required. For composite health care utilization, demonstrating a 3-day difference between the arms with a 6-day standard deviation would detect by a total sample size of 128 patients. With 154 patients, we should have adequate power to detect a difference in our primary outcomes for aims 1 and 2.

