### Patient Enrollment and Randomization

Cardiac surgical patients will be recruited from the Frankel Cardiovascular Center (FCVC) at Michigan Medicine. Opioid-naive patients undergoing first-time, elective cardiac surgery through a full median or miniature sternotomy beginning September 3, 2019, were screened for a targeted enrollment of 154 patients for randomization. Approximately 600 to 750 patients meeting these criteria underwent surgery at Michigan Medicine in 2017. Opioid-naive is defined as opioid-free at the time of preoperative clinic history and physical examination.

Patients lost to follow-up will be censored for data analysis, and missing individual intervention points will be dealt with by multiple imputations, as appropriate. We will compare the clinical and sociodemographic attributes of patients who decline participation and patients lost to follow-up with those of patients with complete follow-up to assess potential responder bias. We estimated a 20% rate of missingness, which was incorporated into our power calculation. On the basis of historical institutional data, we anticipated approaching 5 to 10 patients per week for potential enrollment, with an approximate 5 to 7 month enrollment period within a 12-month study period for completion of clinical follow-up, data analysis, and manuscript production. Although this timeline was affected by the COVID-19 pandemic forcing a pause in enrollment between March 14th and the time of writing, we were 93.5% (144/154) enrolled at the time of pausing and remained optimistic about completing enrollment within our 12-month study period. We used block randomization with randomly variable block sizes generated with Stata 15 software (StataCorp LLC, College Station, TX) and computer randomization occurred with the treatment assignment tool (Treatment Assignment Tool-University of Michigan [TATUM]) from the Michigan Institute for Clinical and Health Research.

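### Minor arithmetic error: the 154-patient target adds 20% to 128 instead of dividing by 0.8, so at 20% missingness power is about 78.5%, not 80%

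*Protocol article*

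**What the plan says.** The Power Analysis section names one primary endpoint, a health care utilization composite "defined as the total number of days spent at home within the first 30 days after surgery". It lists the survey scores (GAD-7, PHQ-9, KCCQ-12, Picker, IES-R, Brief Pain Inventory) and opioid use as secondary.

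Mean days are compared with a two-tailed t test. The authors "set the power of this study at 80% with alpha (Type I error) of .05" and take effect sizes "between medium (0.5) and large (0.8"), "which yields a minimum sample size of 52 patients to detect a large effect size and 128 to detect a medium effect size". A 3-day difference with a 6-day standard deviation is given as the clinical equivalent and again needs 128. Missingness is then added: "Incorporating 20% missingness, a sample size of 154 patients will adequately detect a medium effect size".

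The section on Patient Enrollment and Randomization repeats the point: "We estimated a 20% rate of missingness, which was incorporated into our power calculation". It also says that patients lost to follow-up are censored for the analysis, and it mentions multiple imputation for missing individual intervention points.

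The Power Analysis section closes with: "With 154 patients, we should have adequate power to detect a difference in our primary outcomes for aims 1 and 2".

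**The concern.** A missingness rate is a fraction of those randomised. To be left with 128 after losing 20%, one divides by 0.8. The plan's figure matches multiplication by 1.2 instead, which protects against a smaller loss than the one it states. The 80% power is therefore not delivered under the plan's own assumption.

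The closing sentence raises a second, separate point. It speaks of primary outcomes for two aims, but the same section declares one primary endpoint, which is developed under aim 2, and classes every aim 1 score as secondary. If the sentence is carried into the results paper, null findings on the survey scores could be presented as coming from primary, specifically powered comparisons.

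**Working it through.** **Inputs from the protocol article**

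- Two-tailed t test, alpha 0.05, power 80%, d = 0.5 or 0.8, base totals 128 and 52, and 3 days with SD 6 (3/6 = 0.5): Power Analysis.
- 20% missingness: Power Analysis, and Patient Enrollment and Randomization.
- Target of 154: Power Analysis.
- Allocation ratio: not stated. I assume 1:1; this reproduces the plan's base totals exactly.

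**Step 1. Reproduce the base figures.** Two-sample t test, noncentral t:

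- d = 0.5: 63.8 per arm, so 64 per arm, total 128. Matches.
- d = 0.8: 25.5 per arm, so 26 per arm, total 52. Matches.

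**Step 2. Reproduce the inflated figure.**

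- n × (1 + 0.20) = 128 × 1.2 = 153.6, so 154. Matches the plan.
- n / (1 − 0.20) = 128 / 0.8 = 160. This is the number that leaves 128 after a 20% loss. The difference is 160 − 154 = 6.
- The normal approximation does not explain 154 either: it gives a base of 126, and 126 / 0.8 = 157.5, so 158.

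**Step 3. What 154 delivers at 20% missing.** 154 × 0.8 = 123.2, so about 123 evaluable (61 + 62).

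| Evaluable patients | Power for d = 0.5 (t test) |
|---|---|
| 128 (64 + 64) | 80.1% |
| 123 (61 + 62) | 78.5% |

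The normal approximation gives 79.2% at 61 + 62, also below 80%.

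**Step 4. The same shortfall in other terms.**

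- Largest missingness that leaves 128 evaluable: 1 − 128/154 = 26/154 = 16.9%.
- Effect detectable with 80% power at 61 + 62: d = 0.509. In days, 0.509 × 6 is about 3.06, against the planned 3.

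**Step 5. The claim about aims 1 and 2.** The passages side by side:

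- Primary endpoint: days at home. It is described under Aim 2 and named as the only primary endpoint in Power Analysis.
- Aim 1 instruments: all listed as secondary in Power Analysis.
- Worked examples on a real scale: opioid use (114 patients) and days at home (128 patients). Both belong to aim 2. No aim 1 score is given a standard deviation or a target difference.
- Aim 1 analysis: mean GAD-7, PHQ-9, IES-R and Brief Pain Inventory scores are compared with two-tailed t tests, so the unit-free d = 0.5 calculation does apply to them.

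The sentence therefore conflicts with the endpoint hierarchy in its own section. The aim 1 scores have a generic calculation behind them, but no scale-specific one.

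**The case against.** **The shortfall is too small to matter.** It is 6 patients and about 1.5 points of power, and the detectable difference moves by roughly 0.06 of a day, about 1.3 hours, on an endpoint counted in whole days. The 3-day and 6-day inputs are round planning values and are probably less certain than that. This stands, and it is why the point is minor. A reader might infer that the trial is underpowered in a way that threatens its conclusions; the figures do not support that.

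**Missingness on the primary endpoint may be below 20%.** Days at home comes from chart review as well as conversations with patients, so it does not depend on survey return alone. At 15% missing, power is 81.0%; at 10%, 83.2%. This is fair, but some post-discharge components rely on patient contact, and the plan itself says that its calculation covers 20%.

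**Twenty percent could mean extra enrolment, or imputation could restore the losses.** Neither reading fits the text. The plan calls the figure a rate of missingness. It says that patients lost to follow-up are censored, and it mentions imputation only for missing intervention points.

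**The opioid example survives.** It needs 114 patients, and at 61 per arm its power is about 83%. This stands, but opioid use is a secondary endpoint.

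**The aim 1 claim has some basis.** A reader might infer that nothing in the document supports power for aim 1. That goes too far, because the d = 0.5 calculation is unit-free and applies to the aim 1 scores compared by t test. The sentence can also be read loosely as the main outcomes within each aim. What remains is that the word primary contradicts the single declared primary endpoint.

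**Conclusion.** The point holds as a minor error. The plan adds 20% to 128 where its stated missingness requires dividing by 0.8. As a result, 154 randomised patients give about 78.5% power for d = 0.5 at 20% missing, not 80%; they keep 80% with up to 16.9% missing.

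This rests on 1:1 allocation, on the plan's own effect size and SD, and on missing patients dropping out of the primary comparison, as the censoring statement implies. The direction of the error does not depend on the choice between the t test and the normal approximation.

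The reference to primary outcomes for two aims is a separate labelling conflict and also needs correcting, whatever one makes of the power figure.

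**What to change.** 1. In Power Analysis, replace the sentence on missingness with: 154 randomised patients give about 78.5% power for d = 0.5 with 20% missing, or 80% power with up to 16.9% missing. The alternative, if the 80% claim at 20% missing is to be kept, is a target of 160. That costs 6 more patients; the article reports 144 enrolled and enrolment still ongoing.
2. In the closing sentence, refer to the single primary endpoint, days at home. Add that the aim 1 scores are secondary and are covered only by the generic d = 0.5 calculation, with no scale-specific one.
3. Make the matching sentence in Patient Enrollment and Randomization consistent with item 1.

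Items 1 (as restated for 154), 2 and 3 are wording changes and need no extra patients.

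A covariate-adjusted comparison of days at home could be added as a supporting analysis, but it is optional and should not displace the planned t test. Its gain depends on how much variance the covariates explain, which the document does not give. As an assumption, R² of 0.05 would give 80.6% power at 123 evaluable and R² of 0.10 would give 82.6%, using an effective effect size of 0.5/√(1 − R²). Of the plausible preoperative covariates (for example age, procedure type or preoperative KCCQ-12), only preoperative KCCQ-12 is explicitly scheduled for collection (Table 1).

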## Results

### Preliminary Data

An 11-patient feasibility study in aortic surgery patients (HUM00138828) was performed at the FCVC, 6 of whom were randomized to the control and 5 to the intervention arm. Extremely useful insight from this feasibility trial included feedback from intervention patients regarding the time-points at which their dedicated, trained comfort coach was most beneficial. This feedback was used to solidify the 6 touchpoints for our full clinical trial. In addition, an assumption about utilizing nonpharmacological interventions was that pain management and recovery after surgery were individualized processes. In contrast, we received feedback that family and relatives are intimately involved in patients' healing and emotional well-being. Furthermore, some patients indicated that their family members benefited from the comfort coach interventions, in some instances, even more than the patient. In addition, family interaction and socialization during the perioperative process were identified as important to pain management.

Executing the feasibility trial also provided direct insights for our study team. Using certified child life specialists in dual roles as full-time specialists at the children’s hospital and on-call for the feasibility trial proved to be a barrier to effective intervention, primarily because of the distance between the hospitals creating time-related challenges for meeting each touchpoint. Accordingly, these experiences informed the development of the full clinical trial by highlighting the importance of hiring a full-time, dedicated comfort coach to enhance the number of touchpoints met and increase care continuity. Most importantly, this preliminary trial demonstrated that it would be feasible to perform the comfort coach study protocol at the University of Michigan.

After completing the feasibility study, the study team performed telephone interviews of study patients and former open-heart surgery patients through the FCVC’s Patient Family Advisory Council to gain further insight into the patient experience and use this input to select the most appropriate survey instruments for the full clinical trial.

### Full Clinical Trial

Our clinical trial is funded by Blue Cross Blue Shield of Michigan Foundation, and enrollment is currently ongoing. As of June 2020, 144 patients have been enrolled and randomized in the trial, and 50 semistructured qualitative interviews have been performed. Since March 14, 2020, all survey touchpoints and interviews have been conducted remotely via telephone, online, or mail because of human subject research restrictions implemented at the University of Michigan to limit exposure to patients and staff during the COVID-19 pandemic. Comfort coach touchpoints for patients in the intervention group have continued during their inpatient hospitalization, whereas 30-day follow-up visits with the comfort coach are now conducted remotely. We have completed our qualitative interview process and are currently evaluating our coded data, with plans to publish our qualitative findings by the end of 2020. We anticipate that enrollment, data collection, and analysis will be completed by September 2020 and expect to submit our initial quantitative results for publication by the end of 2020.

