##### Analytic Approach

Mean total GAD-7 and PHQ-9 scores at each of the 4 time-points (Table 1) will be compared between the 2 groups with two-tailed *t* tests, whereas categorical findings (eg, mild, moderate, or severe anxiety on the GAD-7 and minimal, mild, moderate, moderately severe, or severe depression on the PHQ-9) will be compared between groups using chi-square tests. In addition, repeated measures ANOVA (analysis of variance) tests will be performed for the GAD-7 and PHQ-9 across the 4 time-points to examine differences between groups while accounting for correlation over time within each patient. IES-R mean total scores will be compared between groups using a two-tailed *t* test, and the proportion of patients in each group meeting established cutoffs (≥24, ≥33, and ≥37) [64-66] will be compared with chi-square or Fisher exact tests, as appropriate. Chi-square tests will be used for the Picker Patient Experience Questionnaire to determine differences in mean proportions of *problems* reported out of the 15 items in the survey. The mean intrapatient difference between preoperative clinic and 30-day follow-up in functional status scores on the KCCQ-12 will be evaluated (≥5 point difference indicates a clinically important difference) and compared between study cohorts. Pain severity and pain interference scores will be determined (both out of 10) from the Brief Pain Inventory and generated for each patient. These 2 mean scores will be compared between groups using a two-tailed *t* test. Finally, pain score proportions on a 4-point scale (none, minimal, moderate, or severe) recorded through the 30-day postoperative questionnaire will be compared across groups using the chi-square test.

**Table 1 table1:** Schedule of survey instrument administration. The survey administration schedule is indicated for both study cohorts (ie, all patients).

Preoperative clinic visit for History and Physical	Day of discharge	30-day postoperative clinic visit	90-day postoperative clinic visit or phone call
GAD-7^a^	GAD-7	GAD-7	GAD-7
PHQ-9^b^	PHQ-9	PHQ-9	PHQ-9
KCCQ-12^c^	BPI^d^	Picker Patient^e^	N/A^f^
N/A	N/A	IES-R^g^	N/A
N/A	N/A	OPIOID^h^	N/A
N/A	N/A	KCCQ-12	N/A

^a^GAD-7: Generalized Anxiety Disorder 7-item scale.

^b^PHQ-9: Patient Health Questionnaire-9.

^c^KCCQ-12: Kansas City Cardiomyopathy Questionnaire 12-item short-form.

^d^BPI: Brief Pain Inventory.

^e^Picker Patient: Picker Patient Experience Questionnaire.

^f^N/A: not applicable.

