#### Spillover Effects

Our trial may be susceptible to spillover effects, both internally in our intervention and from external forces such as competing institutional interventions. Specifically, opioid reduction efforts for specific general surgery procedures at our institution have demonstrated spillover effects into additional general surgery procedures, with corresponding reductions in opioid use found [83]. Similar efforts around perioperative education and opioid prescribing have taken place in cardiac surgery and may affect the opioid use secondary outcome if current prescribing and use are too low to observe significant changes. Internal spillover effects may also occur, such as nursing and other care team members observing comfort coach interventions and incorporating these nonpharmacological techniques into their usual care. We attempted to mitigate this effect by conducting in-service educational sessions with physicians, advanced practice team members, and nurses to make each stakeholder aware of the trial and the intervention being tested. In addition, if a trend of improvement in the control arm of this trial over time is observed, this difference over time will be treated as the effect size of spillover, and we will report it as such in the trial analysis.

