#### COVID-19 Effect

Approximately 20% of patients during the trial will have received inpatient care either during or after the peak of the COVID-19 pandemic. The usual amount of fear and anxiety elicited by cardiac surgery and the associated recovery period enhance patients’ typical need for close physical, emotional, and psychological support from their loved ones. The hospital-wide policy prohibiting all visits during COVID-19 may cause an increase in the levels of fear and anxiety caused by surgery and recovery owing to enhanced feelings of isolation, separation, and possibly even abandonment—at such a crucial time of need—by the most important loved ones in their lives. These policy changes may enhance the impact of a comfort coach on the intervention arm, simply by adding more human contact through a caring and empathetic individual at these critical touchpoints of care, irrespective of the nonpharmacologic therapy the coach provided.

In contrast, the control patient group during the COVID-19 pandemic may be at a potential disadvantage compared with the control patient group before COVID-19 because the pre-COVID control group had the usual level of support from family, friends, and significant others. These 2 opposing effects, namely, a potential enhancement for the intervention group and additional tension and anxiety from isolation and separation among the control group, may have affected the study results. However, it is also possible that patients in the intervention group during COVID-19 remained anxious and fearful despite having a comfort coach because of separation from loved ones, fear of infection in the hospital, or other factors. Although we cannot mitigate the impact of COVID-19, we will perform a subset analysis of patients who received care during COVID-19 to evaluate for any significant differences in our data.

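### The March 14, 2020 switch to remote surveys overlaps strongly with the COVID-19 period, so the planned COVID-19 subset analysis and the control-arm spillover rule could label a change of survey mode as a pandemic or spillover effect

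*Protocol article*

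**What the plan says.** Table 1 of the protocol article (Aim 1, Analytic Approach) ties the surveys to the preoperative clinic visit, the day of discharge, the 30-day clinic visit and, for the last one, a "90-day postoperative clinic visit or phone call". Under Full Clinical Trial the article then reports that since March 14, 2020 "all survey touchpoints and interviews have been conducted remotely via telephone, online, or mail". Enrollment paused on the same date: "we were 93.5% (144/154) enrolled at the time of pausing".

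Two later statements interpret differences over calendar time:

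- **COVID-19 Effect:** "we will perform a subset analysis of patients who received care during COVID-19 to evaluate for any significant differences in our data". The section puts the share of patients with inpatient care during or after the peak at about 20%. It discusses visitor restrictions, isolation and fear of infection, but not the change in how the scales were collected.
- **Spillover Effects:** the rule begins "if a trend of improvement in the control arm of this trial over time is observed" and goes on to treat that difference as the size of spillover.

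**The concern.** The surveys measure anxiety, depression, stress, patient experience, functional status, and pain and opioid use after discharge. Answers to such items may depend on whether they are given in clinic, to a caller, or alone on paper or online. If they do, the scores shift at March 14, 2020 for a reason unrelated to the pandemic or to staff adopting the coach's techniques.

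The two statements above would then misname the cause. The spillover rule is the firmer problem, because it assigns a single cause in advance and asks only that an improvement be observed. The COVID-19 statement is looser, but a reader would naturally take a difference found there as an effect of the pandemic.

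**Working it through.** **Inputs from the article.** Screening began on September 3, 2019. The switch and the pause both fall on March 14, 2020, which is 193 days later. Enrollment then stood at 144 of 154, and 144/154 = 0.935 reproduces the stated 93.5%. The COVID-19 share is about 20%, and 0.20 × 154 = 30.8, or about 31 patients against 123.

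**Assumptions (the article gives no survey counts by mode).** The 144 patients accrued evenly over the 193 days, the last 10 are surveyed remotely throughout, and discharge is 7 days after surgery. The gap from clinic to surgery is 21 days, which makes the remote share at discharge match the stated 20%; gaps of 7 to 42 days give the range.

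**Step 1: remote share at each survey.** With L the days from enrollment to the survey, share = (144 × L/193 + 10)/154.

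| Survey | L (days) | Remote share | Range |
|---|---|---|---|
| Preoperative | 0 | 6.5% | 6.5% |
| Discharge | 28 | 20% | 13-30% |
| Day 30 | 51 | 31% | 24-41% |
| Day 90 | 111 | 60% | 54-70% |

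If only the 144 are counted (share = L/193, gaps of 7 to 28 days), the shares are 0% preoperatively, 7-18% at discharge, 19-30% at day 30 and 50-61% at day 90.

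**Step 2: overlap of mode with COVID-19 period.** Patients still in hospital on or after March 14 have 100% remote postoperative surveys. Among the other 123:

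- Discharge: 0% remote.
- Day 30: 0.311 × 154 = 48.0 remote in all, less 30.8, leaves 17.2; 17.2/123.2 = 14%.
- Day 90: 0.602 × 154 = 92.7, less 30.8, leaves 61.9; 61.9/123.2 = 50%.

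The difference in remote share between the two groups is therefore 1.00 at discharge, 0.86 at day 30 and 0.50 at day 90.

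**Step 3: apparent effect of a pure mode shift.** For an assumed mode effect m in SD units and no pandemic effect, the pre/post difference is m × (difference in remote share). With m = 0.3 this is 0.26 SD at day 30 and 0.15 SD at day 90.

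**Step 4: chance of a significant pooled pre/post t test (two-sided 5%).** The smaller sample is 20% of the roughly 124 patients left after 20% missingness (25 against 99); the larger is 31 against 123.

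| Assumed m | Day 30 | Day 90 |
|---|---|---|
| 0.2 SD | 12-14% | 7-8% |
| 0.3 SD | 21-25% | 10-11% |
| 0.5 SD | 48-57% | 20-23% |

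**Step 5: between-arm contrasts.** The switch fell on the same date for both randomized arms, so with the same mode mix in each arm its expected contribution to the arm difference is m × 0 = 0.

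**The case against.** Much of the case on the other side stands.

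- **Arm contrasts.** The planned survey analyses compare arms, and a switch common to both does not bias them on average. A reader might infer that within-patient KCCQ-12 change is affected, since "The mean intrapatient difference between preoperative clinic and 30-day follow-up in functional status scores on the KCCQ-12 will be evaluated". The same sentence goes on to compare that change between the study cohorts, so it too is an arm contrast.
- **Primary endpoint.** Days at home is not a survey scale. It comes from chart review and conversations with patients.
- **Overlap.** Mode does not split exactly along the COVID-19 line. Mode follows the survey date and the subset follows the date of care, and a telephone call was already allowed at 90 days.
- **Mode mix by arm.** A reader might infer that it differs, because three remote modes are allowed and only the intervention arm has a remote coach visit at day 30. The article does not say that the coach collects surveys or that mode was chosen by arm. This is a risk to guard against, not a documented bias.
- **Size.** The documents give no mode effect, and neither its size nor its direction is known. A pooled pre/post t test is one reading of the subset analysis, not a test that the plan names.
- **Spillover rule.** It is conditional on improvement and does not name the survey scales; the outcome that its section names is opioid use. Outpatient opioid use is, however, itself collected by the 30-day questionnaire.
- **Deferred detail.** Logging and tabulating mode may sit in a fuller document that is not shown. That answers a complaint about missing detail. It does not answer the spillover attribution, which the article states itself.

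**Conclusion.** The point holds as a limit on attribution. From March 14, 2020, survey mode and COVID-19 period overlap strongly (a difference in remote share of about 0.86 at day 30 and 0.50 at day 90). A pre/post difference on the survey scales could therefore be mode rather than pandemic. A control-arm improvement on those scales would be called spillover whatever its cause.

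With an assumed 0.3 SD mode effect, a pooled day-30 comparison would be significant about 21-25% of the time instead of 5%. That figure rests on the assumed mode effect, even accrual, the assumed gap and stay, and a test that the article does not specify. The direction of the argument does not depend on them.

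The documents do not support a stronger reading, that the switch biases the trial's treatment comparisons or its primary result.

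**What to change.** 1. Record the mode and date of every survey, and tabulate mode by arm and time-point.
2. For surveys still to be collected, use the same order of modes in both arms, with the coordinator collecting them and not during the coach's remote visit.
3. Add a sensitivity analysis of the survey outcomes that either adjusts for mode or uses in-person surveys only. It checks how far results depend on mode. It cannot fully separate mode from the pandemic, because the two overlap so closely.
4. Reword Spillover Effects and COVID-19 Effect so that calendar-time and pre/post-March 14 differences on survey scales are reported as joint effects of pandemic, survey mode and spillover, and are not attributed to spillover or COVID-19 alone.

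The cost is one extra data field, a sensitivity analysis with less precision (the in-person version keeps about 70-80% of day-30 surveys among the 144) and a weaker statement about spillover. No new patients or visits are needed. Mode should be recorded now, since it may be hard to recover later.
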